#### Adverse events

Given that patients with stroke are expected to experience frequent adverse events, we defined our ‘expected’ events *a priori*. These are listed in a checklist at each follow-up. Any other adverse event is also recorded. Our expected serious events are: (1) deaths categorized as vascular (stroke, myocardial infarction, other vascular), infection, fracture, other and (2) Hospitalizations (stroke, myocardial infarction, other vascular, infection, fracture, other).

### Risks to internal validity

The main risks to the internal validity of the trial are ‘contamination’ between treatment groups, threats to the fidelity of the intervention and unblinding. To prevent ‘contamination’ between intervention and control patients in the ward during the hospital stay, we advise that the stroke coordinators delivering the intervention interview patients and carers in a private consulting or treatment room or use curtains around the patient’s bed. The time spent by the routine ward physiotherapist with control and intervention patients is monitored and recorded, to check that there is no systematic bias in routine physiotherapy. To help prevent control patients from viewing the trial manual, the manuals are given to intervention patients at the time of the first home visit and a general stroke booklet (placebo) is given to both groups. The topic of ‘contamination’ forms part of the regular training at site initiation, site visits and annual collaborators’ meetings.

Fidelity of the trial intervention is monitored during site initiation and subsequent site training visits by the clinical coordination team and a consultant physiotherapist contracted to help with training. Logs of all intervention activities are collected and analyzed to summarize the duration of each intervention and the main activities within the intervention. In addition, we will document whether the trial participants were assessed or treated by the usual routine care physiotherapists, and measure the total time spent per patient, to ensure that both intervention and control patients have the same background rehabilitation care.

Blinding is maintained by employing a dedicated blinded outcome assessor for each site. It is a requirement that the blinded outcome assessor not share the same office as the stroke coordinator and has separate computer and scanning equipment. The detailed written intervention guide has been kept confidential from the site principal investigators and blinded outcome assessors at each site. At the annual collaborators’ meetings, there are separate training sessions for the stroke coordinators and blinded outcome assessors, to maintain confidentiality of the intervention details. Patients are asked not to disclose details of home visits to the blinded outcome assessor, and intervention patients are asked to hide the trial manual when the blinded outcome assessors visit. The trial intervention is stopped one month before the first follow-up at 3 months to help reduce unblinding. Any inadvertent unblinding is recorded by the blinded assessor. Examples of unblinding are discussed at the plenary sessions at the collaborators’ meetings to share experiences, and to implement strategies to prevent future occurrences.

### Sample size and statistical consideration

In the meta-analysis of early supported discharge trials, the proportion of people dead or dependent at the end of follow-up was 50 % and the likely beneficial effect of early supported discharge treatment was an odds reduction of 21 % (95 % confidence interval 3–26 %). Therefore, the proposed minimum sample size of 1200 (600 per group) provides at least 90 % power (two-tailed α, 0.05) to detect plausible modest 10.5 % reductions in death or dependency in the intervention group with inflation by 20 % to account for patients dropping out of the trial. Ideally, a higher recruitment will allow a greater precision for treatment estimates, and could permit more detailed subgroup analysis; thus, when 1200 patients have been recruited, and if funding and time permits, the data and safety monitoring committee will advise on whether it is safe to continue recruitment. Experience during 2014 and early 2015 has allowed prediction that the trial will complete recruitment in early 2016, based on current strategies.

The intention to treat principle will be applied in all analysis. The primary endpoint measure is the proportion of those dead or dependent (modified Rankin scale score 0–2) at 6 months. This will be analyzed using an unadjusted logistic regression model. Binary secondary outcomes will be analyzed similarly, using analysis of variance (*t* tests) for continuous variables. For the shift analysis of modified Rankin scale using all seven categories (including 6 for death), ordinal logistic regression will be used, after verifying the proportional odds assumption. A statistical analysis plan will be completed prior to analysis and unblinding of the trial data.

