Although appropriate stroke unit care and rehabilitation may meet important clinical, physical and psychosocial needs during the early post-stroke phase, the needs of patients and families in the long term cannot solely be addressed in hospital [14, 15]. Advocates for early supported discharge and home-based stroke rehabilitation, which is based upon a coordinated stroke unit model of care, argue that it offers several advantages: satisfying patient choice; reducing risks (and costs) associated with inpatient care through reductions in length of hospital stay; a better rehabilitation setting, as the home setting is more focused towards realistic goals, social inclusion and a supportive environment; and leading to savings in direct and indirect costs [16, 17]. Early supported discharge provides a continuous process of rehabilitation that spans the in-hospital period and the weeks of resettlement and readjustment at home. A meta-analysis of 11 trials (mainly conducted in developed countries, where fully funded community rehabilitation teams are available) shows that early supported discharge services significantly reduced the odds of death or dependency by 21 % (odds ratio 0.79; 95 % confidence interval 0.64–0.97), without major adverse effects, either on patients or caregivers [17].

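### The 10.5-point target does not follow from the cited 21% odds reduction: that effect is 5.9 points, for which 1200 patients give about 44–53% power, not 90%

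*Protocol article*

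**What the plan says.** Under Sample size and statistical consideration, the protocol article takes two inputs from the meta-analysis of early supported discharge trials:

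- the event rate: "the proportion of people dead or dependent at the end of follow-up was 50" %;
- the effect: "the likely beneficial effect of early supported discharge treatment was an odds reduction of 21" %.

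The next sentence is presented as following from these. It claims a power of 90% or more, at a two-sided alpha of 0.05, from 1200 patients in two equal groups. The effect for which that power is claimed is given in these words: "to detect plausible modest 10.5 % reductions in death or dependency in the intervention group". The total is said to include a 20% allowance for dropout.

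The Background reports the same meta-analysis and leaves no doubt about the scale: early supported discharge "significantly reduced the odds of death or dependency by 21 % (odds ratio 0.79; 95 % confidence interval 0.64–0.97").

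The primary endpoint is to be analysed by unadjusted logistic regression, so the odds ratio is also the scale of the primary result.

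**The concern.** An odds reduction and a risk reduction are close only when the event is rare. At 50% they differ by almost a factor of two. The article cites 21% on the odds scale and then powers the trial for a 10.5% reduction, and 0.50 × 0.21 = 0.105 exactly. That product is what one gets by treating the 21% as a relative reduction in risk.

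If so, the trial is sized for a much larger effect than the one given as its rationale. A reader would take the chance of missing the meta-analytic effect to be at most 10%, when it is about one half. A neutral result could then be taken as evidence against family-led rehabilitation when the trial had little ability to detect the benefit it set out to find. The steering committee and the data and safety monitoring committee would also lack the true power when considering recruitment beyond 1200, which the same section allows for.

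**Working it through.** **Inputs.** Control rate p1 = 0.50, odds ratio 0.79, two-sided alpha 0.05, power 90%, 600 per group and 20% inflation for dropout, all from the sample size section (the odds ratio is also in the Background). Allocation is 1:1 (Randomization section). With 20% lost, 600 × 0.8 = 480 per group are analysed.

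**Formulas.** With d = p1 − p2, p̄ the mean of p1 and p2, A = 1.960 × √[2p̄(1 − p̄)] and B = √[p1(1 − p1) + p2(1 − p2)]:

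- n per group for 90% power = (A + 1.2816 × B)² / d²
- power = Φ[(d√n − A) / B]

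**Step 1: reproduce the plan's figure.** Read 10.5% as absolute points, so p2 = 0.395 and p̄ = 0.4475. Then A = 1.378 and B = 0.699.

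- n = (1.378 + 0.896)² / 0.105² = 469.2, so 470 per group.
- Allowing for 20% loss, 470 / 0.8 = 588 per group, 1176 in total. With a continuity correction it is 489, then 612 per group, 1224 in total. Both are close to 1200.
- Power with 480 per group is 90.6%.

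The plan's figure is reproduced for an absolute difference of 10.5 points. Read as a relative reduction (50% to 44.75%), 10.5% would have power of only 37% (480 per group) to 44% (600 per group), so the absolute reading must be the one used.

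**Step 2: what 10.5 points means on the odds scale.** The control odds are 1, so the odds ratio is 0.395 / 0.605 = 0.653, a 35% odds reduction.

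**Step 3: what the cited effect means on the risk scale.** p2 = 0.79 / 1.79 = 0.4413. The absolute reduction is 0.50 − 0.4413 = 0.0587, or 5.9 points (11.7% relative).

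**Step 4: power for the cited effect.** p̄ = 0.4707, A = 1.3835, B = 0.7047.

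- 480 per group: (0.05866 × 21.909 − 1.3835) / 0.7047 = −0.140, power 44.4%.
- 600 per group: (0.05866 × 24.495 − 1.3835) / 0.7047 = 0.076, power 53.0%.
- n for 90% power: (1.3835 + 0.9031)² / 0.05866² = 1,520 per group analysed, or 1,520 / 0.8 = 1,900 per group (3,800 in total) with 20% loss.

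| True effect (control 50%) | Odds ratio | Power, 480 per group | Power, 600 per group |
|---|---|---|---|
| 10.5 points (39.5%) | 0.65 | 90.6% | 95.6% |
| 7.5 points (42.5%) | 0.74 | 64% | 74% |
| 5.9 points (44.1%) | 0.79 | 44.4% | 53.0% |

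With 480 per group, 90% power is reached only at about 10.4 points (odds ratio about 0.66), and 80% at about 9.0 points (odds ratio about 0.70).

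**Step 5: sensitivity.**

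- A Wald test of the log odds ratio, matching the planned logistic model, gives 44.4% and 53.0%.
- If 50% is the average of both arms (52.9% vs 47.1%), power is 44.6% and 53.2%.
- If the inflation was done by multiplying by 1.2, 500 per group are analysed and power is 45.9%.
- Control rates of 30%, 40%, 60% and 70% give 37–44% power with 480 per group and 44–52% with 600, so a different event rate does not rescue the claim.

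**Step 6: the cited interval.** The Background's odds ratio interval of 0.64–0.97 is an odds reduction of 3–36%. The sample size section prints 3–26%. The 35% odds reduction in step 2 is just inside the first and outside the second. On the second, the best case is an odds ratio of 0.74, for which power is 64–74% (table). No effect within the interval printed in the sample size section reaches 90%.

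**The case against.** The strongest reply is that the stated power is not wrong. The article claims 90% for a 10.5% reduction, and for 10.5 absolute points that is right. It never literally claims 90% for an odds ratio of 0.79. This stands: the fault lies in the link between the cited effect and the target. But the article itself makes that link, by presenting the target as the consequence of the two meta-analytic figures and calling it modest.

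Second, the multiplication of 50% by 21% is not shown, and the full protocol might hold a separate reason for 10.5 points. The mechanism is indeed an inference. It is the only derivation the text supports, though, and the finding does not depend on it: whatever its origin, 10.5 points does not follow from the stated inputs.

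Third, 1200 is described as a minimum, and recruitment might continue. That provision is conditional and is justified by precision and subgroup analysis. It would have to bring the analysed total to about 3,040 to restore 90% power.

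Fourth, the correction would change neither the planned size, nor the endpoint, nor the analysis, and how a neutral result is to be interpreted can be left to the statistical analysis plan. Both points are fair. They bear on the cost and place of the remedy, not on whether the justification is wrong as printed. That readers would over-read a neutral result is a prediction, but an inflated power statement invites it.

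**Conclusion.** The concern holds. The sample size section derives a 10.5-point target from a 21% odds reduction that, at a 50% event rate, amounts to 5.9 points. The target is an odds reduction of 35%, about two-thirds larger than the effect cited (35/21 = 1.67). Power for the cited effect is about 44% if the full 20% is lost and 53% if nobody is, where the text leads the reader to expect at least 90%.

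The result assumes a control rate of 50%, 1:1 allocation and a two-sided 5% test, all as stated in the article. It is insensitive to the choice of test, to how the dropout inflation is read, and to control rates between 30% and 70%. The printed justification for the primary outcome should be corrected.

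**What to change.** Restate the justification along these lines: *With 1200 patients and allowing for 20% loss, the trial has 90% power for an absolute reduction of 10.5 percentage points in death or dependency (50% to 39.5%, odds ratio 0.65). For the meta-analytic odds ratio of 0.79 (50% to 44.1%, 5.9 points), power is about 44% with 20% loss and 53% with none.*

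Remove the wording that presents 10.5 points as the consequence of the meta-analysis, and the description of it as modest. Reconcile the interval of 3–26% in this section with the 0.64–0.97 in the Background, which corresponds to 3–36%.

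State, here or in the statistical analysis plan before unblinding, that a neutral result will be interpreted by whether its confidence interval excludes an odds ratio of 0.79.

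The cost is rewording and a less favourable power statement. No extra patients and no change to endpoint or analysis are needed. Powering the trial for an odds ratio of 0.79 at 90% would instead mean about 3,800 patients.

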## Methods

The ATTEND study is a multicentre, prospective, individually randomized, blinded outcome assessed, controlled trial (prospective, randomized, open, blinded, endpoint design) of early supported discharge with a trained family-led caregiver.

The intervention is a stroke rehabilitation package of care that starts in hospital and continues at home, compared with usual care, in at least 1200 patients with mild to moderate disability recruited from 14 hospital sites across India.

The inclusion criteria are:Adults (≥18 years);Recent (<1 month) acute ischaemic, haemorrhagic or undifferentiated stroke;Residual disability (requiring help from another person for everyday activities);Expected to survive to discharge from hospital, with a reasonable expectation of 6 month survival (i.e. not palliative, no evidence of widespread cancer etc.);Able (or by proxy) to provide informed consent.

Exclusion criteria are:Unable to identify a suitable family-nominated caregiver for training and subsequent delivery of care;Unwilling or unable to adhere to follow-up.

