### Randomization

Eligible patients are identified by the trial stroke coordinator (usually a physiotherapist) and medical coordinator. A patient information sheet (Additional file 1) is shared with the patient and nominated caregiver, and outlines the study objectives and risks and benefits to the patient or caregiver. Informed consent from each participant and his or her caregiver is obtained based on the International Conference on Harmonisation Good Clinical Practices guidelines (ICH/GCP) and ethical guidelines for biomedical research on human participants published by the Indian Council of Medical Research, New Delhi (Fig. 1). If the caregiver changes by the time of the 3- or 6-month follow-up periods, the new caregiver will be asked to provide consent for the caregiver aspects of follow-up after reading the patient information sheet. Stroke patients often do not have the capacity to consent, owing to the acute effects of stroke. Capacity for informed consent is assessed by the medically qualified principal investigator at each site. The ethics committee have approved ATTEND to obtain consent from a legally acceptable representative in such cases. Once consented, patients are randomized by the trial stroke coordinator to the intervention or control arm in a 1:1 ratio within 7 days of hospital admission, using a secure, central, password-protected, web-based system, stratified by centre and stroke severity.

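### Allocation is stratified by centre and stroke severity, but the primary model is fixed as unadjusted: a conservative test and a modest, avoidable loss of efficiency

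*Protocol article*

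**What the plan says.** Under Randomization, the protocol article allocates patients "in a 1:1 ratio within 7 days of hospital admission" through a central web system, "stratified by centre and stroke severity". Methods gives the number of centres: patients are "recruited from 14 hospital sites across India".

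Under Sample size and statistical consideration, the primary endpoint is the proportion dead or dependent at 6 months, and the model is named: "This will be analyzed using an unadjusted logistic regression model". The next sentence adds: "Binary secondary outcomes will be analyzed similarly". No stratified or adjusted analysis of any outcome is described. A statistical analysis plan is promised before analysis and unblinding.

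**The concern.** Stratified allocation makes the arms agree closely on centre and severity. To the extent that these factors predict death or dependency, this removes part of the chance variation between arms. An unadjusted logistic model does not know this and still counts that variation in its standard error. The interval is then wider than the design warrants, and the test rejects less often than 5% under the null.

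The trial takes the trouble to stratify across 14 sites and then gives up part of the benefit. Severity is a plausible predictor of death or dependency, and choosing it as a stratification factor suggests that the investigators thought so too. What is at stake is efficiency: a wider interval, and a somewhat larger chance of missing a real effect.

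**Working it through.** **Inputs from the protocol article.** 1:1 allocation; 14 centres; 600 per group; two-sided α 0.05; power at least 90%; control rate 50%; a 10.5% reduction; 20% drop-out; a cited odds reduction of 21%.

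**Assumed, because the article does not give them.** Number of severity levels (2 or 3), permuted blocks of 4, and prognostic strength of severity and centre (a range).

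**Step 1. Reproduce the plan's figure.** Read as 10.5 points, the comparison is 50% vs 39.5%, with mean 0.4475.

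n per arm = [1.960·√(2·0.4475·0.5525) + 1.282·√(0.50·0.50 + 0.395·0.605)]² / 0.105² = 470 (rounded up).

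Dividing by 0.8 gives 588 per arm, 1,176 in total (1,224 with continuity correction), which agrees with 1,200. With 20% lost, 600 × 0.8 = 480 per arm are analysed and power is 0.906. So the stated power holds for an unadjusted comparison.

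**Step 2. Approximation.** Let R² be the share of outcome variance explained by the strata, d the risk difference, p̄ the mean risk, and se₀ = √(2p̄(1−p̄)/480). The unadjusted test uses se₀, but under stratified allocation the difference varies with se₀√(1−R²). Then:

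- true α, unadjusted = 2[1 − Φ(1.96/√(1−R²))]
- power, unadjusted = Φ((d/se₀ − 1.96)/√(1−R²))
- power, adjusted = Φ(d/(se₀√(1−R²)) − 1.96)

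For 50% vs 39.5%, d/se₀ = 0.105/0.0321 = 3.27. A 21% odds reduction from 50% gives 0.79/1.79 = 44.1%, so d/se₀ = 0.0587/0.0322 = 1.82.

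| R² | True α, unadjusted | Power at 39.5%, unadj. / adj. | Power at 44.1%, unadj. / adj. |
|---|---|---|---|
| 0 | 0.050 | 0.905 / 0.905 | 0.445 / 0.445 |
| 0.02 | 0.048 | 0.907 / 0.911 | 0.444 / 0.452 |
| 0.05 | 0.044 | 0.911 / 0.919 | 0.443 / 0.463 |
| 0.10 | 0.039 | 0.917 / 0.932 | 0.442 / 0.484 |
| 0.20 | 0.028 | 0.929 / 0.955 | 0.438 / 0.530 |
| 0.30 | 0.019 | 0.941 / 0.974 | 0.434 / 0.586 |

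**Step 3. Simulation.** 960 analysed, 14 centres, blocks of 4 within each centre-by-severity stratum, Wald tests, and marginal risks held at the stated values. The adjusted model has centre and severity as fixed effects. There were 8,000 runs for the two-level type I error and 39.5% columns, and 3,000 elsewhere. Entries are unadjusted / adjusted, in per cent.

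| Severity effect; centre SD (logit) | Type I error | Power at 39.5% | Power at 44.1% |
|---|---|---|---|
| 2 levels, OR 2; 0.3 | 4.2 / 4.9 | 91.4 / 92.4 | 45.0 / 47.6 |
| 2 levels, OR 3; 0.5 | 3.8 / 5.4 | 91.8 / 93.9 | 43.4 / 49.0 |
| 2 levels, OR 5; 0.5 | 3.3 / 5.5 | 92.4 / 95.2 | 42.7 / 52.4 |
| 3 levels, 0.5 log-odds per level; 0.3 | 4.2 / 5.1 | 91.7 / 92.8 | 44.3 / 47.2 |
| 3 levels, 1.0 per level; 0.4 | 3.1 / 5.1 | 92.4 / 95.2 | 45.0 / 53.2 |
| 3 levels, 1.5 per level; 0.5 | 2.3 / 6.0 | 93.8 / 97.0 | 42.0 / 57.0 |

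At 39.5% the differences run from 1.0 to 3.2 points. At 44.1% they run from 2.6 to 15.0 points. With 3,000 runs the Monte Carlo standard error is about 0.4 points on a 5% rate and 0.9 points on a power near 45%. The adjusted fixed-effects Wald test runs at or slightly above 5% in the stronger scenarios, so a small part of its gain there comes from that.

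**The case against.** **The plan is valid as written.** A pre-specified unadjusted model is transparent, needs no decision about small centres, and estimates a marginal odds ratio. Its error is on the safe side. All of this stands, and it limits the point to efficiency.

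**The size is uncertain.** Prognostic strength is not given. Entry criteria limited to mild to moderate disability and expected 6-month survival narrow the severity range. At the mild end little is lost, and if the strata were not prognostic nothing would be. Three levels at 1.0 or 1.5 log-odds each imply odds ratios of about 7 and 20 between the extremes (e² and e³), which is strong. Losses to follow-up also loosen balance within strata: for 1.0 per level, removing 20% at random gave a type I error of 4.3% in one run, against 3.0% with complete strata. These objections stand, so a range is given.

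**A stronger reading is tempting.** With a conditional odds ratio of 0.65, unadjusted power falls to about 83% or 68% under the two stronger three-level scenarios. A reader might infer that the unadjusted analysis breaks the 90% claim. It does not. As severity becomes more prognostic, that conditional odds ratio means treated risks of 41.1% and 42.3%, or 8.9 and 7.7 points instead of 10.5. Much of the fall is a smaller effect. At the planned risks, unadjusted power stays above 90%.

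**The analysis plan is still to come.** Supportive adjusted analyses may properly be left to it. But the article does not leave the primary model open: it states that the model is unadjusted. Only that choice is criticised here. The article does not say whether the ordinal shift model carries covariates, so this point does not extend to it.

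**Conclusion.** The point holds as a modest loss of efficiency. If the strata are prognostic, the unadjusted test is conservative, with true type I error of about 2% to 5% depending on the assumed strength. Adjustment recovers about 1 to 3 points of power at 50% vs 39.5%, and about 3 to 15 points at 50% vs about 44%. The upper ends need strongly prognostic strata.

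The article does not support reading this as bias, as inflated type I error or as a failure of the stated power. The trial's low power at the cited 21% odds reduction (about 44% at 480 per arm) comes from the gap between that effect and the 10.5-point target, which is a separate matter. It bears on this point only because the avoidable loss is larger there.

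**What to change.** Before unblinding, and in the analysis plan, make the primary model logistic regression of death or dependency on treatment, adjusted for stroke severity as used in the randomization and for centre. State in advance how small centres are handled, for example by a random centre effect or a pooling rule. Report a standardised risk difference beside the odds ratio, and keep the unadjusted model as supportive. Treat the binary secondary outcomes the same way.

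No new data are needed, since both factors are recorded at randomization. The cost is a short change of text, the small-centre rule and one extra estimate to program. The adjusted odds ratio is conditional on the strata and is not the same quantity as the marginal one. The standardised risk difference keeps a marginal effect in view.

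The sample size need not change.
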